### Participant timeline

2.8

Figure 3 presents a timeline systematically detailing the timing of data collection and measurement analyses.

**Figure 3 fig3:**
[figure not shown]
Flowchart of treatment phases. pGGN: pure ground-glass nodule; CJG: Chuanjie Granule; TCM: Traditional Chinese Medicine; BAI: Beck Anxiety Inventory; BDI-II: Beck Depression Inventory-II; SF-36: 36-item Short Form Health Survey.

### Sample size calculation

2.9

The primary outcome was the difference in changes in the maximum diameter of pGGNs before and after treatment. Based on preliminary pre-experimental results showing mean ± standard deviation (SD) differences of 1.11 ± 2.12 mm (intervention group) and 0.19 ± 1.25 mm (control group), sample size was determined using PASS software (version 2021). With a two-sided *α* = 0.05, 1-*β* = 0.90, 1:1 allocation ratio, and accounting for an anticipated 10% dropout rate, a minimum of 86 participants per group is required.

### Minimal clinically important difference (MCID)

2.10

This study prioritizes the MCID over mere statistical significance to assess clinical relevance of the primary outcome. Using a distribution-based method, the MCID is calculated as 0.5 times the SD. By incorporating findings from preliminary pilot data and aiming to eliminate variability that may be attributed to the treatment effect itself, the SD of changes in the pGGN maximum diameter in the control group was used, setting the MCID threshold at 0.63 mm.

### Randomization and blinding procedures

2.11

A centralized randomization system, administered by an independent contract research organization (CRO), will facilitate participant allocation and drug distribution across subcenters. Participants will be randomized in a 1:1 ratio to either the intervention (A) or control (B) groups, employing a stratified block randomization approach. Initially, participants will be placed into an assignment pool. A fixed block size of four will be utilized, incorporating six allocation permutations: AABB, ABAB, ABBA, BAAB, BABA, and BBAA. The random number sequence (1–6) necessary for assigning permutations in chronological order will be generated using SPSS version 28.0. Upon confirmation of eligibility and receipt of written consent, subcenters will request allocation numbers from the CRO. The complete sequence will be retained exclusively by the CRO, with assignments sealed in sequentially numbered opaque envelopes stored in locked cabinets. A strict triple-blind design will be used, keeping participants, investigators, and statisticians unaware of group assignments. After locking the clinical database, the first unblinding will reveal A/B group distinctions but not treatment details. The second unblinding will occur after statistical analysis to reveal treatment assignments. Coded drug kits will be linked to emergency envelopes, and emergency unblinding will require steering committee approval, with implementation verified by treating physicians.

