Control Group: Participants in the control group will be administered a matched placebo. This placebo, produced by the same manufacturer, is composed primarily of maltodextrin and food-grade coloring agents. It is designed to be indistinguishable from the CJG in terms of appearance (color and shape), odor, and packaging. The instructions for administration are identical to those provided to the intervention group.

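### Section 2.11 defines A as intervention and B as control, then releases the A/B labels before the analysis as if they were masked, so the statistician blind lapses from the first unblinding to the end of the analysis

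*Protocol article*

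**What the plan says.** All the relevant statements are in section 2.11 (Randomization and blinding procedures) of the protocol article.

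- **Arm labels:** "Participants will be randomized in a 1:1 ratio to either the intervention (A) or control (B) groups".
- **Randomisation list:** it is built from blocks of four in the same letters, "incorporating six allocation permutations: AABB, ABAB, ABBA, BAAB, BABA, and BBAA".
- **Who is blind:** "A strict triple-blind design will be used, keeping participants, investigators, and statisticians unaware of group assignments".
- **First step, once the database is locked:** "the first unblinding will reveal A/B group distinctions but not treatment details".
- **Second step:** "The second unblinding will occur after statistical analysis to reveal treatment assignments".

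The section also says that the CRO alone keeps the full sequence. It does not say that the letters are recoded before the first release.

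**The concern.** A two-step unblinding has one purpose: to let the analyst compare two groups without knowing which is which. That works only if the labels given out at the first step carry no meaning. Here the labels have a published meaning, given a few sentences earlier in the same section. The statements that the labels hide treatment and that statisticians are unaware of assignment cannot both stand beside that definition.

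Triple blinding is claimed in the Abstract, the Introduction, section 2.1 and section 2.11, and the Discussion counts it among the trial's safeguards against bias. If the procedure is followed as written, the third of the three blinds is missing in the one phase that the two-step release is meant to protect. Any judgement left to the analyst in that phase would be made with the arms known.

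**Working it through.** No figure in the plan bears on this point, so the check is one of logic: set the statements side by side, then see what is left to judgement while the labels are open.

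**1. What the letters mean.** Section 2.11 fixes A = intervention and B = control. The permutations confirm that these are the letters of the list itself: a block of four with two of each letter has 4!/(2! × 2!) = 6 arrangements, and the section lists six.

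**2. What is known at each stage, as written.**

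| Stage | Labels available to the analyst | Is the arm known? |
|---|---|---|
| Up to database lock | None; the CRO alone holds the sequence | No |
| First unblinding to end of analysis | A or B for each participant | Yes, from the definition in section 2.11 |
| After the second unblinding | Treatment | Yes, but nothing is added |

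The arm is a known one-to-one function of the label. Once the label is given, no uncertainty about the arm is left for the second step to remove.

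**3. What it would be with neutral codes.** If X and Y are mapped to the arms at random, there are two possible mappings, each with probability 1/2. The analyst can run every comparison and still not know which group received the active product, unless the results suggest it. The second step then discloses something.

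**4. How many allocations are affected.** The planned enrolment is 172 (86 per group, sections 2.1 and 2.9). If the labels released are the list letters, all 172 are identified at the first step.

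**5. What remains open to judgement in that interval (section 2.14).**

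- *Maximum diameter:* a linear mixed model with a random subject intercept; group, time point and their interaction as fixed effects; age and baseline diameter as covariates. This is largely fixed in advance.
- *Other continuous variables:* t-test or Mann–Whitney U test, tied to the result of normality tests. This is mostly rule-driven, although the normality test and its threshold are not named.
- *Full analysis set against per-protocol set:* both are analysed, and differences between them are weighed on clinical and statistical grounds. This is openly a matter of interpretation, with no rule given.

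The exposure is therefore greatest in the third item, smaller in the second, and small in the first.

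**The case against.** The strongest reply has three parts.

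**The intent is plain.** The section says that the first release is not meant to disclose treatment and that a separate later step does so. The letters in brackets may be no more than shorthand for explaining the block permutations, and the codes actually released may be different. A journal article need not describe how codes are scrambled. It is also true that the text does not name the statistician as the person who receives the labels; that follows only from the analysis falling between the two steps. What stands: a different set of codes may be intended. But this is more than missing detail. The article gives the key and then treats the same letters as masked, and an unseen analysis plan cannot make a published key secret again.

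**The blind is not absent.** A reader might infer that the statistician is never blind. The text does not support that. The CRO alone holds the sequence and the first release follows database lock, so data collection, cleaning and lock are covered. Nor does the A/B problem touch the blinding of participants or investigators during the trial. This part of the reply stands in full.

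**The consequence is modest.** The diameter model is set out in advance and the choice between t-test and rank test is tied to a normality test. This also stands. It limits the harm but does not remove the contradiction.

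A reader might go further and infer from section 2.6 that the participants' blind is weak too, because the placebo description, "It is designed to be indistinguishable from the CJG in terms of appearance (color and shape), odor, and packaging", does not mention taste. The document does not support that inference. It calls the placebo matched, gives its composition only in its main components, and says nothing about taste either way. Silence in a condensed article does not show a mismatch, and this point makes no claim about it.

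**Conclusion.** The concern holds for a limited period. As written, section 2.11 contradicts itself: the labels disclosed at the first unblinding identify treatment, the second unblinding is empty, and the claim of "keeping participants, investigators, and statisticians unaware of group assignments" fails for the statistician from the first unblinding to the end of the analysis. It holds before database lock.

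This rests on two readings of the text, both plain but neither stated outright: that the A/B labels released are the A/B letters already defined, and that the analyst receives them. If separate masked codes are in fact used, the defect is one of wording only.

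The size cannot be put as a bias in millimetres or as a change in error rate. On the plain reading every one of the 172 planned allocations is known during the analysis, with the evaluation of differences between analysis sets and the secondary analyses most exposed. The correction should be made, but the flaw does not by itself undermine the main diameter analysis.

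**What to change.** Amend section 2.11 to say that:

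1. At the first unblinding, after database lock, the CRO releases neutral group codes (for example X and Y) to the statistician.
2. These codes are mapped to the arms at random and independently of the A/B letters of the randomisation list. A fixed relabelling such as A to X would only move the problem.
3. The CRO holds the key until the analysis is final, including the written evaluation of any differences between the full analysis set and the per-protocol set.

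The randomisation list, the coded drug kits and the emergency envelopes need no change, because the recoding takes place only when the labels are released for analysis. It can be done at any time before database lock. The cost is a few sentences in the protocol and one random mapping by the CRO.

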### Withdrawal criteria

2.5

The occurrence of a serious adverse event (SAE) in which continued participation presents a greater risk than benefit;Inadequate compliance, characterized by a failure to adhere to the prescribed medication regimen or the utilization of additional non-protocol therapies for pulmonary nodules;Loss to follow-up during the study period or voluntary withdrawal for any reason.

Upon cessation of treatment or withdrawal from the study, participants will transition into a follow-up phase. The long-term efficacy concerning pulmonary nodules will be evaluated through chest CT findings at the one-year follow-up. Notably, participants whose nodules demonstrate growth meeting established criteria for surgical intervention or who receive a confirmed cancer diagnosis requiring anti-cancer therapy upon completion of the 3-months treatment course will be discontinued from further efficacy follow-up.

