#### Safety outcomes

2.7.3

Safety outcomes will be evaluated through the continuous surveillance of adverse symptoms and physical signs, supplemented by a comprehensive analysis of all scheduled laboratory tests and electrocardiograms (ECGs) conducted during study visits. Specifically, symptoms and signs will be monitored at each patient interaction, including both scheduled visits and any unscheduled communications. Laboratory and ECG safety parameters will be evaluated at baseline, 3 months following the intervention or at the time of early withdrawal, and 1-year observational period after treatment. Additionally, participants who reports symptoms suggestive of a potential adverse reaction during the course of the drug administration will be subjected to immediate unscheduled laboratory testing as clinically indicated. All adverse medical events will be meticulously documented in Case Report Forms (CRFs) within 24 h of occurrence, detailing clinical presentations, time of onset, duration, severity (graded according to CTCAE v5.0), interventions, outcomes, and causality assessment in relation to the trial drug. Trial termination will be considered when participants required additional concomitant medications, surgical interventions, or other physical therapy targeting pulmonary nodules.

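### Section 2.11 makes every emergency unblinding depend on prior steering committee approval, with no stated bypass, which undermines the purpose of the kit-linked emergency envelopes

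*Protocol article*

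**What the plan says.** Section 2.11 of the protocol article sets out who holds the code and how it may be read:

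- **Who is blind.** The design is triple-blind, "keeping participants, investigators, and statisticians unaware of group assignments".
- **Who holds the code.** "The complete sequence will be retained exclusively by the CRO".
- **The emergency device.** "Coded drug kits will be linked to emergency envelopes".
- **The condition on using it, and the treating physician's part.** In the same sentence, "emergency unblinding will require steering committee approval, with implementation verified by treating physicians".

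The only other unblinding steps described are the two planned ones, after database lock and after the statistical analysis. The steering committee is mentioned nowhere else in the article.

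**The concern.** A kit-linked emergency envelope exists so that one participant's allocation can be read quickly, without disturbing the blind for anyone else. The approval condition adds a decision by another body before it may be used. As worded, the condition applies to every emergency, and the physician facing the emergency has no stated authority to open the code.

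What is at stake is patient safety: how soon a physician who needs to know whether a participant is on active product or placebo can find out. The statistical result is not at stake. The question is who may access the randomisation code and in what order the steps come, and it touches no dose, treatment or stopping rule.

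**Working it through.** The article gives no figure on this point, so there is nothing to reproduce or recompute. The sample size of 86 per group is not an input. The check is a reading of section 2.11 against the rest of the article.

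1. **Is the approval condition absolute?** The wording is "emergency unblinding will require steering committee approval". No clause limits it to some cases, and no exception for urgency follows. It is a positive requirement.

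2. **Does it come before the code is read?** Approval authorises the step, and implementation follows and is what physicians verify ("with implementation verified by treating physicians"). The order is therefore approval, then opening, then verification. The physician appears only at the last stage.

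3. **Is there another route to the code?** Section 2.11 keeps the full sequence with the CRO alone ("The complete sequence will be retained exclusively by the CRO"), and investigators are blinded. A search of the remaining sections for unblinding, envelopes and the steering committee finds no bypass, response time, standing availability or right to open first and report later.

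4. **Does the protocol foresee situations in which the code could be wanted urgently?** Yes. Section 2.5 lists as a withdrawal reason "The occurrence of a serious adverse event (SAE) in which continued participation presents a greater risk than benefit". Section 2.7.3 says that participants whose symptoms suggest a reaction during dosing are to be "subjected to immediate unscheduled laboratory testing as clinically indicated". Neither section mentions access to the code, so neither supplies another route. Neither makes its own action wait for the committee either.

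5. **What follows?** The time from an emergency to reading the code has at least two parts: the time to obtain approval and the time to open the envelope. The rule makes the first part compulsory, and the article puts no upper limit on it. Without prior approval, only the second part remains.

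**The case against.** The strongest reply is that the two halves of the sentence are compatible. The envelope is the means, committee approval is the authorisation, and an envelope opened after approval works as intended. The article also condenses a fuller protocol and refers to SOPs and GCP. Contact times, delegation to one member or approval by telephone may be set out there. Prior approval also restrains unnecessary code breaks.

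Much of this stands, and it rules out several stronger readings that a reader might infer:

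- **That the rule defeats the envelopes, or withholds the code.** It does not. It delays access by an authorisation step, and approval is not refusal.
- **That it contradicts section 2.7.3.** It does not. Laboratory testing needs no treatment code, and withdrawal under section 2.5 turns on risk against benefit. These sections show that urgent events are foreseen, and nothing more.
- **That the committee sits away from the sites or cannot respond at any hour.** The article says nothing about its membership, location, quorum or availability.
- **That committee involvement harms the blind.** Knowing that a code was sought does not reveal the allocation, and the article does not say that the committee learns the result. The fixed blocks of four do not help this argument. With two A and two B in a block, one known A leaves one A and two B, so each of the other three is B with probability 2/3 and A with probability 1/3. That holds for any code break, however authorised, and only for someone who knows which participants share the block.

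The appeal to condensation does not dispose of the point. It excuses details left out, whereas this is a rule put in. A fuller document could shorten the approval step, but direct access for the physician would conflict with the sentence as published.

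**Conclusion.** The point holds in a limited form. Section 2.11 makes every emergency unblinding conditional on prior steering committee approval, gives treating physicians only a verifying role and states no bypass. This adds a compulsory step of unstated length before one participant's code can be read, and so undermines the purpose of the emergency envelope.

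The size of the delay cannot be derived from the document. It could be short if approval is delegated and always available, and longer if it is not. The conclusion does not depend on which is true. It rests on the wording of the requirement and on the absence of any exception elsewhere in the article. It shows no internal contradiction, no harm to the blind and no effect on the primary estimate, error rate or power. It is best classed as a cheap improvement for patient safety.

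**What to change.** Amend the sentence in section 2.11 so that:

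- an emergency code break for a single participant does not depend on prior committee approval;
- the result goes only to the physician who needs it, and not to the radiologists, the statisticians or other site staff;
- the CRO and the steering committee are notified afterwards, with the reason documented;
- prior committee approval is kept for non-emergency unblinding.

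The cost is one sentence in the protocol and a short addition to site training. The downside is a few more code breaks without prior review, which notification and documented review afterwards help to control. Sample size, analysis and treatment are unaffected.

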### Quality control and data management

2.12

The trial adhered to the ethical principles outlined in the Declaration of Helsinki, the International Council for Harmonization (ICH) Good Clinical Practice (GCP) guidelines, and relevant Chinese regulatory requirements (22, 23). To ensure the quality of trial implementation, all participating investigators underwent training on the study protocol and Standard Operating Procedures (SOPs) during the project initiation phase. Training covered protocol-based inclusion/exclusion criteria, case report forms (CRFs) completion, investigational product compliance, and standardized AE reporting.

Paper-based CRFs recorded baseline subject data and visit results, with dual data entry and real-time validation for accuracy. An electronic data capture system standardized data management, accessible only to authorized personnel with tracked modifications for verification. The Research Ethics Committee audited data quality, drug safety, and project progress. Major protocol deviations prompted emergency reviews to ensure trial quality and data security.

### Trial status

2.13

Subject recruitment for this clinical trial is anticipated to commence in September 2025.

### Statistical analysis

2.14

Data analysis will be conducted utilizing IBM SPSS Statistics version 28.0 (IBM Corp., Armonk, NY, United States). Efficacy analyses will encompass all patients who are randomly assigned (full analysis set, FAS; adhering to modified intention-to-treat principles) as well as all patients who completed the trial protocol (per-protocol set, PPS). Any discrepancies between the FAS and PPS analyses will be evaluated from both clinical and statistical standpoints. The safety analyses will be based on the safety set (SS), which includes all patients who received at least one dose of the investigational drug. All hypothesis tests will be two-tailed, with a significance threshold set at *α* = 0.05. *p*-values will be calculated from the relevant statistical tests, with *p* ≤ 0.05 being regarded as statistically significant.

To conduct a longitudinal comparison of the trajectories of changes in the maximum diameter of pGGN relative to baseline across various groups at follow-up time points, a linear mixed model will be utilized. This model will incorporate random subject intercepts to account for within-subject correlations arising from repeated measurements. The fixed effects will include group, follow-up time points, and their interaction, while covariates will consist of age and baseline pGGN maximum diameter. For other continuous variables, intergroup comparisons will be performed using independent samples t-tests for normally distributed data or Mann–Whitney U tests for non-normally distributed data, contingent upon the results of normality tests. Categorical variables will be compared using chi-square tests or Fisher’s exact tests. To assess the potential impact of distinct clinical characteristics on treatment efficacy, predefined subgroup analyses will be conducted, considering factors such as gender, age, smoking status, number of lung nodules, and risk stratification. Interaction tests will be performed to investigate whether differences in efficacy between groups vary across these subgroup factors.

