#### Primary outcome

2.7.1

The primary outcome, the change in the maximum diameter (ΔD) of the pGGN from baseline, which will be calculated using the following formula:

ΔD=Bmax−Pmax

Where: *Bmax* = baseline maximum diameter and *Pmax* = post-treatment maximum diameter.

Measurements will adhere to the 2017 Fleischner Society guidelines for pulmonary nodule assessment (16). For participants with multiple nodules, the maximum diameter of the nodule with the highest risk or the largest size will be measured. In cases where multiple nodules share an identical maximum diameter, the nodule will be selected for measurement following risk stratification, prioritizing the highest-risk nodule. The analysis of CT images will be conducted by two independent board-certified radiologists, each possessing relevant clinical expertise. Using lung window settings (window width: 1400 HU; window level: −700 HU), the pGGN will be identified, and its maximum diameter will be measured on the transverse slice where it appears largest. Triplicate measurements will be conducted for each nodule at each time point, and the average value will be calculated and recorded in millimeters (mm), rounded to the nearest integer. Assessments will be performed at baseline, at 3 months (end of treatment), and at 1 year (end of follow-up).

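### The primary outcome has two follow-up visits and a trajectory model, but no visit or contrast is named as the test that decides the trial

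*Protocol article*

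**What the plan says.** Three sections of the protocol article bear on this.

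- **Section 2.7.1 (Primary outcome)** defines the outcome as baseline minus post-treatment maximum diameter and gives its schedule: "Assessments will be performed at baseline, at 3 months (end of treatment), and at 1 year (end of follow-up". Neither follow-up visit is ranked above the other.
- **Section 2.9 (Sample size calculation)** sizes one quantity, "the difference in changes in the maximum diameter of pGGNs before and after treatment", from pilot "mean ± standard deviation (SD) differences of 1.11 ± 2.12 mm (intervention group) and 0.19 ± 1.25 mm (control group". It names no visit for these figures.
- **Section 2.14 (Statistical analysis)** compares the course of change over the follow-up visits with a linear mixed model: "The fixed effects will include group, follow-up time points, and their interaction", adjusted for age and baseline diameter. On correlation it says: "This model will incorporate random subject intercepts to account for within-subject correlations arising from repeated measurements". It gives no residual covariance structure. The 0.05 two-sided threshold applies to all hypothesis tests.

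**The concern.** The model in section 2.14 yields at least four tests of treatment: the group main effect, the group-by-visit interaction, the difference at month 3 and the difference at year 1. They answer different questions, and the article does not say which one decides. The deciding test could therefore be settled after the results are known.

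The interaction is the most literal reading of a comparison of trajectories, and it is the least suitable. The outcome is already change from baseline and there are only two post-baseline visits. The interaction therefore asks whether the effect differs between month 3 and year 1, not whether there is an effect.

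A second, conditional issue is the covariance. A random intercept with independent residuals assumes the same variance of change at both visits. If the two variances differ, the standard errors of the separate visit contrasts are wrong, and a visit contrast is what section 2.9 appears to size.

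**Working it through.** **Inputs from section 2.9.** "With a two-sided *α* = 0.05, 1-*β* = 0.90, 1:1 allocation ratio"; effect 1.11 − 0.19 = 0.92 mm; SDs 2.12 and 1.25 mm; "accounting for an anticipated 10% dropout rate"; 86 per group.

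**1. Reproducing the stated sample size.**
- V = 2.12² + 1.25² = 6.057, so the root-mean-square SD is √(6.057/2) = 1.740 mm.
- Normal approximation: n = (1.960 + 1.282)² × 6.057 / 0.92² = 75.2, so 76 per group; 76/0.90 gives 85.
- Two-sample t-test (noncentral t, pooled or Welch): 77 per group; 77/0.90 = 85.6, so 86. This matches exactly.

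The trial is therefore sized for a difference in mean change at one time point. With 77 evaluable per arm, SE = √(6.057/77) = 0.280 mm and 0.92/0.280 = 3.28. Power is 90.7% by normal approximation and 90.2–90.3% by t-test.

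**2. Power of each candidate test.** Assumptions: month-3 effect 0.92 mm, SD 1.740 at both visits, 77 per arm, complete data, between-visit correlation ρ from 0.3 to 0.9. Variances:
- either visit: V/77
- main effect: (V/77)(1 + ρ)/2
- interaction: (V/77) × 2(1 − ρ)

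| Effect at year 1 | Month 3 | Year 1 | Main effect | Interaction |
|---|---|---|---|---|
| 0.92 mm (sustained) | 91% | 91% | 92–98% | 5% |
| 0.46 mm (halved) | 91% | 38% | 71–86% | 28–96% |
| 0 (gone) | 91% | 5% | 39–53% | 79–100% |

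Under a sustained effect the interaction contrast is 0.92 − 0.92 = 0, so its power equals its type I error.

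**3. Type I error if more than one test may count.** This is the probability that either of two correlated normal statistics exceeds 1.96 in absolute value.
- Month 3 or year 1: 9.1% at ρ = 0.5 and 8.3% at ρ = 0.7. Over ρ = 0.3 to 0.9 the range is 9.5% down to 7.0%. Independent tests would give 1 − 0.95² = 9.75%.
- Any of the four tests: about 11–13% (simulation, ρ = 0.3 to 0.9).

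**4. The common-variance assumption.** Let k be the year-1 SD divided by the month-3 SD. The article gives no value, so k is assumed. With complete data and independent residuals, the model uses the average of the two visit variances. The month-3 SE is then multiplied by f = √((1 + k²)/2), and the year-1 SE by f/k. Month-3 power is Φ(3.28 − 1.96f).

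| k | Month-3 SE factor | Month-3 power | Month-3 type I error | Year-1 SE factor | Year-1 type I error |
|---|---|---|---|---|---|
| 0.75 | 0.884 | 94% | 8.3% | 1.179 | 2.1% |
| 1 | 1.000 | 91% | 5.0% | 1.000 | 5.0% |
| 1.25 | 1.132 | 86% | 2.7% | 0.906 | 7.6% |
| 1.5 | 1.275 | 78% | 1.2% | 0.850 | 9.6% |
| 2 | 1.581 | 57% | 0.2% | 0.791 | 12.1% |

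There is no error at k = 1, and the direction reverses below 1.

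**The case against.** **Month 3 is already implied.** Section 2.7.1 uses the post-treatment diameter and labels 3 months as the end of treatment. Section 2.9 refers to before and after treatment. Section 2.5 treats the one-year CT as long-term efficacy, and section 2.1 describes that year as observational without study drug. This stands as far as it goes: a reader might infer that the trial has no intended primary time point, and the text does not support so strong a reading. Nor does anything make year 1 a declared co-primary endpoint. But section 2.7.2.2 applies the same post-treatment diameter at both 3 months and 1 year, so the term does not single out a visit. Month 3 is implied, not fixed.

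**The error figures depend on rules that the article does not state.** This is true. It does not say that either visit suffices, or that the interaction decides. The figures show what the open choice permits, not what will happen.

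**Covariance detail belongs in an analysis plan.** Largely fair. A reader might infer that the model is bound to give a wrong standard error, and the article does not support that:
- It states neither a year-1 SD nor a residual structure.
- Section 2.5 ends efficacy follow-up for participants who reach surgical criteria or need cancer therapy after the 3-month course, which could move the year-1 spread either way.
- With complete data the main effect and the interaction keep correct standard errors whatever the visit variances; only the separate visit contrasts are affected.
- The unequal pilot SDs of the two arms are no evidence of a problem. With 1:1 allocation, pooling the arm variances leaves the SE of a visit difference at √(V/77) = 0.280.

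What remains is a conditional remark. Which visit and contrast decide the trial is a different matter: it is part of defining the primary outcome and belongs in the protocol.

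**Conclusion.** The point holds for the unnamed deciding test and should be settled before unblinding. Sections 2.7.1, 2.9 and 2.14 respectively give two unranked visits, one sized difference and a trajectory comparison, and none says which test decides. Letting either visit count would put family-wise error at about 8–9% for assumed correlations of 0.5–0.7. Letting the interaction decide would leave 5% power against a sustained 0.92 mm benefit. The power figures rest on the pilot SDs applying at both visits, 77 evaluable per arm and no allowance for covariate adjustment.

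The variance point is secondary and conditional. At an assumed SD ratio of 1.5, month-3 power would be about 78% and year-1 type I error about 9.6%. At a ratio of 1 nothing is lost, and below 1 the month-3 test becomes the liberal one. The sample size itself is not in question if month 3 is the named visit.

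**What to change.** 1. State in sections 2.7.1 and 2.14 that the single primary test is the between-arm difference in change in maximum diameter at month 3, estimated from the mixed model, and state in section 2.9 that the sample size refers to this contrast.
2. Make the year-1 difference a secondary test, carried out at 0.05 only if the month-3 test is significant. Report the main effect and the interaction as descriptive.
3. Replace the random intercept with an unstructured within-subject covariance over the two visits, so that each visit contrast uses its own variance. Arm-specific variances are not needed for this purpose.

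The cost is a few sentences and one covariance option in the mixed-model procedure. No participants or visits are added, and 86 per group still gives about 90% power. The downside is that the year-1 result is secondary and cannot by itself carry a positive trial. Section 2.13 expected recruitment to begin in September 2025, and section 2.11 keeps the statisticians blinded, so the clarification can still be made without knowledge of results if it is dated before unblinding.
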